### Participants

Inclusion criteria for CYPRO comprise adult age (≥ 18 years), definite PPMS diagnosis, Expanded Disability Status Scale (EDSS) score  ≤ 6.0, and signed consent [21–23]. Exclusion criteria concern severe lower extremity spasticity or concomitant disease states (i.e., orthopaedic, cardiovascular, metabolic, psychiatric, other neurological, serious medical conditions) that would impair the ability to participate. Pregnant or breastfeeding women or those intending to become pregnant are excluded. Further, pwPPMS are prohibited to participate, if they regularly perform HIIT (i.e., ≥ 2 times per week), if non-compliance is suspected, if they are not able to follow study procedures (e.g., due to insufficient German literacy), or in case of a recent treatment change (e.g., change in disease-modifying treatment (≤ 6 weeks), stem cell treatment (≤ 6 months)). PwPPMS are excluded from further participation in case of severe adverse events (e.g., cardiovascular decompensation) during cardiopulmonary exercise testing (CPET) at baseline, sudden severe disease progression, or falling sick (e.g., due to bacterial or viral infections) during the participation in CYPRO.

### Recruitment and randomization procedure

All pwMS entering the Valens rehabilitation clinic for an inpatient stay are screened for study eligibility. Eligibility screening is performed as a two-step process. In the first step, PPMS diagnosis and EDSS score are checked in advance of clinic admission. In the second step, all other eligibility criteria are checked by in-person consultation on the day of clinic admission. Sixty-one pwPPMS will be recruited. As the sex ratio in pwPPMS is 1:1, we pursue recruiting an equal number of female and male pwPPMS [14]. The number of screened pwMS in total and per screening step, as well as reasons for ineligibility are documented.

Stratified randomization to either HIIT or MCT (1:1) is performed by a group of blinded investigators not involved in CYPRO. Allocation sequence generation is performed using random-sized (block size 4–6) permuted block randomization with Randomization-In-Treatment-Arms (RITA) software (Version 1.51, Evident, Lübeck, Germany). To ensure allocation concealment, the blinded investigators are called for assignment each time a participant presents for inclusion [24]. CYPRO study personnel that performs enrolment, obtains consent, and assigns participants has no access to details on the allocation sequence and blocking. Strata include relative V̇O_2peak_ (mL · min^-1^ · kg-^-1^) at baseline, sex, age, and EDSS score.

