### Sample size calculation

Sample size calculation for the estimated effect of HIIT or MCT on the primary outcome V̇O_2peak_ was performed using G*Power software (Version 3.1.9.7, Heinrich Heine Universität, Düsseldorf, Germany) [20]. Estimating a drop-out of 15%, a total of 61 participants (HIIT: *n*= 30, MCT: *n*= 31) was found to be sufficient to identify a small to moderate effect (*ES* ≥ 0.15) in ANOVA analysis on 2 group (HIIT vs. MCT) * 2 time (T_0_ vs. T_4_) interaction. Power was set at 80% and alpha at 0.05. Correlation among repeated measures was set at 0.6.

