### Statistical analysis

Statistical analyses are performed according to the intention-to-treat principle. Descriptive statistics will be reported as arithmetic mean (*M*) and standard deviation (*SD*) for continuous data, and as absolute number and percentage (*%*) for categorical data for the total sample, and separated by group. Outcome data will be checked for normality (Shapiro-Wilk test) in advance. If necessary, analyses will be adjusted accordingly. If missing values are < 5%, ANCOVA will be performed to detect time*group interaction effects and main effects of time. In that case, effect sizes will be calculated as partial eta squared (*pη*^*2*^). Otherwise, a baseline-adjusted Mixed Model for Repeated Measures (MMRM) approach, with group, time and the group × time interaction as fixed effects (type III sums of squares, CS covariance structure over time) is used to assess between-group differences over time. Bonferroni-corrected pairwise comparisons of estimated marginal means of the group × time interaction are computed. Effect sizes will be reported as Cohen’s *d* with 95% confidence interval (*CI*). For all analyses, the level of significance is set at *p* = .05. Within-group differences and between-group differences are depicted as point estimates and measures of variability for all outcomes. Bivariate correlation analyses will be conducted to determine potential associations between changes in V̇O_peak_, PPO, walking capacity, cognitive performance, HRQoL, fatigue, anxiety and depressive symptoms, and blood-based biomarkers using Pearson’s *r*. All statistical analyses will be conducted with IBM SPSS Statistics for Windows (Version 29.0., IBM Corp., Armonk, New York, USA). Besides the final analysis, one interim analysis will be performed upon collection of 50% of participant data (HIIT: *n* = 15, MCT: *n* = 16).

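### The stated MMRM leaves out three of the four stratification factors (sex, age and EDSS), which makes the test conservative and costs power if those factors are prognostic

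*Protocol article*

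**What the plan says.** Under Recruitment and randomization procedure, the protocol article describes stratified 1:1 allocation by "random-sized (block size 4–6) permuted block randomization". The strata are relative VO2peak "at baseline, sex, age, and EDSS score". The article gives no cut-offs or number of levels.

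The Statistical analysis section names two models and chooses between them by the amount of missing data:

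- **Missing values under 5%:** an ANCOVA, with no covariate named.
- **Otherwise:** a baseline-adjusted MMRM "with group, time and the group" by time interaction as fixed effects, with the type of sums of squares and the covariance structure also fixed.

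The Sample size calculation section allows for 15% drop-out, and the Compliance section says that people who drop out have no later assessments. The Baseline variables section already provides for recording sex, age and EDSS.

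**The concern.** Factors used to constrain the randomisation should normally be in the analysis. Stratification makes the arms more alike on those factors, so the treatment estimate varies less from one allocation to another. A model without the factors does not see this. It leaves their variance in the residual and reports a standard error that is too large.

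Here one of the four factors, baseline VO2peak, enters the primary MMRM through the baseline adjustment. The other three do not. For secondary outcomes such as walking or cognition, baseline adjustment most naturally means that outcome's own baseline value. On that reading none of the four factors enters those models.

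At stake is power in a small trial, from variables that will be on file anyway.

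**Working it through.** **Which model applies.** 61 × 0.85 = 51.9, so about 52 completers. Planned loss of 15%, with no later assessments after drop-out, exceeds the 5% threshold. The MMRM is therefore the branch to expect.

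**The plan's own figure.** The inputs are "small to moderate effect (*ES* ≥ 0.15) in ANOVA analysis on 2 group" by 2 time interaction, 80% power, alpha 0.05 and correlation 0.6. Reading the effect size as Cohen's f, the noncentrality is λ = f²·N·2/(1 − ρ) on 1 and N − 2 df. This needs 72 completers, or 72/0.85 ≈ 85 randomised, so 61 is not reproduced. That is a separate matter and nothing below rests on it.

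**A difference for the illustration.** With the same reading, f = 0.15 in a 2 × 2 interaction is a difference in change of 4 × 0.15 = 0.6 SD. After adjustment for a baseline correlated at 0.6, the residual SD is √(1 − 0.36) = 0.8. The difference is 0.6/0.8 = 0.75 residual SD. It remains an assumption, because the article does not define its effect size.

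**Hand check without adjustment.** The standard error with 52 completers is 2/√52 = 0.277 residual SD. Then 0.75/0.277 = 2.70, which on 49 df gives power of about 75%.

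**Simulation.** 61 people, four two-level factors with equally likely levels, blocks of 4 or 6 within the 16 strata, and 52 completers. The outcome is analysed by a linear model with group and baseline, with and without the other three factors. With one follow-up time, this stands in for the baseline-adjusted MMRM. The share of residual variance (after baseline) that sex, age and EDSS jointly explain is not in the document and is varied.

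| Share explained | Actual SD of estimate, unadjusted | Mean reported SE, unadjusted | Mean reported SE, adjusted | Type I error, unadj. v adj. | Power, unadj. v adj. |
|---|---|---|---|---|---|
| 0% | 0.278 | 0.278 | 0.282 | 4.9% v 5.0% | 76% v 75% |
| 10% | 0.268 | 0.278 | 0.267 | 4.1% v 5.5% | 75% v 77% |
| 20% | 0.267 | 0.279 | 0.253 | 3.8% v 5.2% | 76% v 82% |
| 30% | 0.254 | 0.279 | 0.236 | 3.2% v 5.3% | 76% v 86% |

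The unadjusted standard error stays near 0.279 while the true spread shrinks. At 30% it is 0.279/0.254 = 1.10 times too large. Simulation error at 6,000 runs is about 0.3 points for type I error (√(0.05 × 0.95/6000)) and 0.6 points for power (√(0.75 × 0.25/6000)). A second set of runs gave powers within 2 points of those shown (75% v 73%, 77% v 79%, 75% v 82%, 77% v 87%).

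**Strata and balance.** Four factors give at least 2⁴ = 16 strata, so 61/16 = 3.8 people each on average, below the smallest block. Even so, with 16 strata the mean arm difference in the share at one level of a factor is 5.6 percentage points, against 10.4 under simple randomisation. A gap of 20 points or more occurs in 0.4% of runs against 13%. Arm sizes differ by 7 or more in 15% of runs, against 0% with unstratified blocks.

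**The case against.** **The article is a condensed account.** A full covariate list may stand in the full protocol or an analysis plan. This holds for the ANCOVA branch, which names no covariates, so a reader who infers that the three factors are in no model at all goes beyond the text. It does not hold for the MMRM, whose fixed effects are listed together with its covariance structure. That is a stated choice.

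**The gain may be small.** What counts is what sex, age and EDSS explain beyond the outcome's own baseline over three weeks, and the document gives no figure. If the share is 0 to 10%, the change in power is about −1 to +2 points. This stands for the primary outcome, where baseline VO2peak is already adjusted for. The case is stronger at 20% or more, which is possible but not shown.

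**Stronger readings that the document does not support:**

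- A reader might infer from 3.8 people per stratum that the blocks cannot balance the factors. At 16 strata they roughly halve the imbalance of simple randomisation. Most of the benefit would be lost only with many more strata (with 54: 8.7 points, and gaps of 20 or more in 7% of runs), and the article does not give the number. All that can be said is that the planned 30/31 split is not secured; unequal arms of this order cause no bias and cost little power.
- A reader might infer that the result is biased or the test too liberal. Allocation is random with respect to the factors, so the estimate is unbiased, and the error in the test is on the conservative side.
- A reader might conclude that the randomisation method should change. Recruitment was under way, with 23 enrolled by March 2023, and a switch during the trial is a debatable trade-off that this point does not require.

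**Conclusion.** The point holds for the MMRM. Three of the four stratification factors are missing from the primary model and, if baseline means each outcome's own value, all four from the secondary models. The consequence is a conservative test and lost precision. At an assumed 0.75 residual SD and 52 completers, adjustment changes power by about −1 point if the factors explain nothing, and by +2, +6 and +10 points if they explain 10, 20 and 30% of the residual variance. The sizes rest on those assumed shares, on equally likely two-level factors, and on reading the effect size as Cohen's f. The omission does not threaten the validity of the trial. It is a modest and inexpensive improvement that should be made.

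**What to change.** In the Statistical analysis section, prespecify sex (categorical), age and EDSS (both continuous) as covariates in the primary and all secondary models. Include them alongside the outcome's own baseline value and baseline relative VO2peak (continuous; for the primary outcome these two are the same variable). Apply this in both the ANCOVA and the MMRM branches, whatever imbalance is observed, and settle it before the interim analysis. If the factors are to be left out, give the reason.

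The cost is one sentence and 3 degrees of freedom in the primary model, or 3 + 1 = 4 in secondary models where baseline VO2peak is also added. If the factors explain nothing, about 1 to 2 points of power are lost. No new data are needed, since all four variables are already planned baseline measurements.

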### Exercise protocols

Within their three-week inpatient stay at the Valens rehabilitation clinic, participants perform two to three weekly HIIT or MCT sessions on bicycle ergometers (Cybex 750 C, Cybex International Inc., Massachusetts, USA) in addition to standard rehabilitative care. Standard rehabilitative care comprises endurance and strength training (30-45 minutes, three to five times per week), physiotherapy to improve balance and/or walking ability (30 minutes, daily) as well as occupational therapy focused on fatigue management and activities of daily living (30 minutes, two to three times per week). Exercise volume of HIIT and MCT protocols have been matched in Units of Exercise. Units of Exercise are calculated as [intensity (percentage of peak heart rate (%HR_peak_)) x session duration (minutes) x frequency (number of sessions per week) x number of weeks] [25]. %HR_peak_ is derived from HR_peak_ achieved during CPET at baseline. During sessions, HR is continuously recorded by HR sensors (H10 HR sensor, POLAR, Kempele, Finland) attached to chest belts, and connected to wristwatches (M430 sports watch, POLAR, Kempele, Finland). Both, HIIT and MCT are conducted under the supervision of trained exercise scientists and physiotherapists, either individually or in small groups of up to three participants. Therapists are instructed to monitor the HR, and to adjust pedaling resistance in case of deviations from the target intensity. If participants are unable to follow the prescribed protocols (e.g., due to pronounced ankle flexor spasticity), dose modifications (i.e., decreasing revolutions per minute (rpm) or interval duration, increasing break duration) are permissible. Any dose modification is documented in a case report form. Blinding of therapists and participants towards group allocation is not feasible due to the study design.

#### High-intensity interval training (HIIT)

HIIT sessions commence with a two-minute low-intensity warm-up (60%HR_peak_) at 60-70 rpm. Subsequently, six 90-second high-intensity intervals (95%HR_peak_) are performed at high pedaling rates of 80-100 rpm. Intervals are interspersed by 90-second active breaks with unloaded pedaling at 60-70 rpm, aimed to return to 60%HR_peak_. Sessions close with a two-minute low-intensity (60%HR_peak_) cool-down of unloaded pedaling at 60-70 rpm. In total, one HIIT session lasts 21 minutes.

#### Moderate-intensity continuous training (MCT)

MCT represents the standard treatment at Valens rehabilitation clinic and is used as an active comparator. Participants perform continuous bicycle ergometry at moderate intensity (60%HR_peak_) and pedaling rates of 60-70 rpm for the duration of 26 minutes.

#### Safety considerations

Exercise is safe in pwMS and not associated with a higher risk of adverse events compared to exercise in healthy individuals [26]. Similarly, HIIT on bicycle ergometers is well-tolerated and holds a low risk of adverse events in pwMS [27]. As in healthy individuals, transient knee and/or leg pain, or muscle soreness may occur in response to HIIT and MCT sessions. Between HIIT and MCT sessions, participants receive at least 48 hours of rest to ensure adequate recovery. Supervising therapists are instructed to prevent, monitor, and document the occurrence of adverse events, if any. To prevent injuries or falls, participants may be assisted in getting on and off the bicycle ergometer, if necessary. HR monitoring, rating of perceived exertion (RPE, Borg Category Ratio-10-point (Borg CR-10) scale), and observation of vegetative signs serve to minimize any risk of overexertion [28]. Study personnel may need to withdraw participants in case of repeatedly reported adverse events (e.g., leg pain), the occurrence of severe adverse events (e.g., cardiovascular decompensation), or other medical reasons (e.g., infections). In those cases, participants are forwarded to a physician for medical clearance. With the signature of the consent form prior to participation, participants confirm that they are informed about potential exercise-related risks and the right to refrain from participation in CYPRO at any time.

### Outcomes

V̇O_2peak_, PPO, walking capacity, cognitive performance, HRQoL, fatigue, and anxiety and depressive symptoms are assessed by allocation-blinded outcome assessors at study entry (baseline, T_0_) and discharge after three weeks (T_4_), at least 48 hours after the last HIIT or MCT session. Venous blood samples are taken before (T_1_), immediately after (T_2_), and two hours after (T_3_) the first HIIT or MCT session, and at T_4_.

#### Baseline variables

Demographic data (sex, age) and MS-related data (EDSS score, time since diagnosis (months), pharmacological treatment, if any) are obtained from medical records. Bodyweight is determined by digital scales (Soehnle Style Sense Comfort 100, Soehnle, Nassau, Germany) at fasted state without footwear. Body weight (kg) and self-reported body height (cm) are used to calculate the body mass index (BMI). Cognitive status at baseline is evaluated using the Montreal Cognitive Assessment (MoCA). The MoCA is 30-point test used to assess global cognitive status, including items addressing short-term memory, visuospatial abilities, executive functions, attention, concentration, working memory, language, and orientation. A MoCA score < 26 indicates cognitive impairment [29]. Sensitivity and specificity to discriminate between cognitively impaired and non-impaired pwMS have been proven [30]. MoCA performance does not influence the eligibility to participate in CYPRO.

#### Cardiorespiratory fitness

V̇O_2peak_ is assessed by CPET on a bicycle ergometer (ergometrics er800s, ergoline GmbH, Bitz, Germany). CPET is performed in a fasted state between 8:00 and 9:00 AM and follows a ramp-type protocol. The ramp-type protocol consists of (a) a resting state measurement without pedaling while participants are sitting on the bicycle ergometer (3 minutes); (b) subsequent pedaling at 20 watts (3 minutes); (c) the testing phase with a progressive increment of 5 to 10 watts per minute until subjective exhaustion (8-12 minutes); (d) followed by a cool-down of unloaded pedaling (3 minutes). HR is continuously monitored. Blood pressure and RPE (Borg CR-10 scale) are assessed every two minutes and within the last ten seconds of the test.

V̇O_2_ is monitored by direct and continuous measurements (breath by breath) by ergospirometry (Vyaire Medical, Vyntus CPX, Illinois, USA). V̇O_2peak_ is defined as the highest 15-second averaged V̇O value when the following criteria are attained: respiratory equivalent ratio > 1.10; HR_peak_ within 10 min^−1^ of the age-predicted maximum and Borg-CR-10 rating > 8.5 [31]. The absolute V̇O_2peak_ value (mL · min^−1^) is divided by bodyweight (kg) to obtain the relative V̇O_2peak_ value (mL · min^− 1^ · kg^− 1^) as the primary outcome.

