Alongside ongoing efforts to improve disease-modifying treatment in pwPPMS, optimization of complementary non-pharmacological treatment options is recognized as essential to maintain and improve the health-related quality of life (HRQoL) in pwPPMS [7]. Accordingly, the International Progressive MS Alliance called upon action, proposing symptom management and rehabilitation as one key priority area for research in progressive MS [8]. In line with the proposed goals for MS therapies, endurance training qualifies as an effective means to improve HRQoL, numerous MS symptoms, such as walking impairment or fatigue, and MS-related performance impediments, such as reduced cardiorespiratory fitness, in pwMS [8–10]. Beyond that, high-intensity interval training (HIIT) has been described to beneficially modulate systemic concentrations of blood-derived biomarkers relevant to PPMS pathophysiology. For example, an acute HIIT session reduced concentrations of serum neurofilament light chain (sNfL), serving as a surrogate marker of disease progression, neuroaxonal damage, and CNS atrophy [11, 12]. Additionally, HIIT has been shown to shift systemic concentrations of neurotoxic and pro-oxidant metabolites towards neuroprotective metabolites of the immunomodulatory and neuroactive kynurenine pathway (KP) [11, 13].

However, results have been obtained from mixed samples, dominated by RRMS phenotype. The generalizability of training designs and the desired beneficial effects of endurance training on the subpopulation of pwPPMS remains unclear, given that PPMS presents with distinct clinical features, such as progressive spastic paraparesis as a hallmark symptom [14, 15]. Owing to the high prevalence of progressive spastic paraparesis, particularly pwPPMS may be prone to physical deconditioning, which is indicated by low cardiorespiratory fitness. As cardiorespiratory fitness is associated with HRQoL, walking impairment, cognitive performance, fatigue, and potential CNS tissue sparing in pwMS, improvement of cardiorespiratory fitness represents a key research outcome in MS trials and constitutes a central target in MS rehabilitation [10, 16].

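### Read literally, the primary outcome exists only when three maximal-effort criteria are all met, although the exercise test ends at subjective exhaustion and no value is defined for a test that misses one

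*Protocol article*

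**What the plan says.** All references are to the protocol article.

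- **Outcome definition (Cardiorespiratory fitness).** V̇O2peak is the highest 15-second average "when the following criteria are attained: respiratory equivalent ratio > 1.10; HR_peak_ within 10 min" per minute "of the age-predicted maximum and Borg-CR-10 rating > 8.5". The value divided by bodyweight is the primary outcome. The criteria are joined by a semicolon and an *and*. There is no *or*, no *two out of three*, and no value for a test that misses one.
- **End of test (same section).** The ramp is a "progressive increment of 5 to 10 watts per minute until subjective exhaustion". Reaching the criteria is not the stopping rule.
- **Randomization (Recruitment and randomization procedure).** Relative V̇O2peak at baseline is a stratification factor, with sex, age and EDSS score.
- **Eligibility and withdrawal (Participants).** EDSS may be up to 6.0, and severe lower-extremity spasticity is excluded. Missing the effort criteria is neither an exclusion nor a withdrawal reason.
- **Analysis (Statistical analysis).** Intention to treat. ANCOVA is used if fewer than 5% of values are missing, otherwise a baseline-adjusted MMRM.
- **Population (Background).** PPMS has distinct features "such as progressive spastic paraparesis as a hallmark symptom", and "particularly pwPPMS may be prone to physical deconditioning, which is indicated by low cardiorespiratory fitness".
- **Sample size (Sample size calculation).** 61 participants, allowing for 15% drop-out.

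**The concern.** The three criteria are checks that a maximal effort was reached. Used as a condition on the primary outcome, they turn a test of insufficient effort into a missing value.

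In a leg-limited, deconditioned population a cycling test may end before heart rate comes near the age-predicted maximum. Such a test has been run as the protocol requires and has produced a highest 15-second average, but under the printed definition it has no V̇O2peak.

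Three things are at stake:

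- **Baseline.** A participant without a baseline value cannot be placed in a stratum and has no baseline to adjust for.
- **Who is analysed.** Losses would tend to fall on the more disabled participants, which narrows the group to which the result applies and departs from intention to treat.
- **Freedom of choice.** If the handling of such tests is not settled, it could be decided after results are known.

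**Working it through.** **1. The provisions side by side**

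| Provision | Needs a V̇O2peak for everyone? | Does the definition supply it? |
|---|---|---|
| Stratification on baseline V̇O2peak | Yes, before allocation | Only if all three criteria are met |
| Eligibility and withdrawal rules | Do not remove participants who miss a criterion | No value for them |
| Intention to treat | Yes, for everyone tested | Only if all three criteria are met at that visit |
| Peak power output, from the same test | Not applicable | Defined without any criteria |

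The last row shows the oddity: one test can give a valid peak power output and no V̇O2peak.

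**2. How often could a test miss a criterion?** The article gives no rate. To see what the heart-rate criterion alone could do, assume that peak heart rate minus prediction is normal with mean −b and standard deviation s, and that the criterion fails when the shortfall exceeds 10 beats/min. Then P(fail) = Φ((b − 10)/s). The values of b and s are assumptions.

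| Mean shortfall b | s = 10 | s = 15 |
|---|---|---|
| 0 | Φ(−1.00) = 16% | Φ(−0.67) = 25% |
| 10 | Φ(0) = 50% | Φ(0) = 50% |
| 20 | Φ(1.00) = 84% | Φ(0.67) = 75% |

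With b = 0 and s = 5 the figure is Φ(−2) = 2%. The other two criteria can only add failures. The range is so wide that it establishes plausibility and nothing more.

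**3. The plan's own sample size.** Inputs from the Sample size calculation section: f = 0.15 (the stated effect size, read as Cohen's f because G*Power's ANOVA is used), correlation 0.6, two time points, alpha 0.05, power 80%. For the group-by-time interaction, λ = f² × N × 2 / (1 − 0.6), with 1 and N − 2 degrees of freedom.

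- N = 72 gives λ = 0.0225 × 72 × 2 / 0.4 = 8.10 and power 80%. That is 72 evaluable, or 72/0.85 = 84.7, so 85 with drop-out. The stated 61 is not reproduced.
- The plan's 61 less 15% is 61 × 0.85 = 51.85, so about 52 completers. There λ = 5.85 and power is 66%.

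The gap from 80% to 66% is a separate sample-size matter and is not charged to this point.

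**4. Additional loss from the outcome rule.** Assume that 60 to 85% of the 52 completers meet the criteria at both visits: 0.60 × 52 = 31 and 0.85 × 52 = 44. With the formula in step 3:

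| Valid pairs | λ | Power | Loss from 52 pairs |
|---|---|---|---|
| 52 | 5.85 | 66% | – |
| 44 | 4.95 | 58% | about 8 points |
| 31 | 3.49 | 44% | about 22 points |

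These are powers for a comparison of change in complete pairs. The 15% allowance is for drop-out and contains nothing for tests that miss the criteria.

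**The case against.** **No section says that a test missing a criterion is discarded.** Stratifying on baseline V̇O2peak, and having no related eligibility rule, both fit a practice in which every test yields a value and the criteria serve as effort checks. This is a fair reading of intent, but it is not what the definition says. If it is the intent, the sentence still needs correcting.

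**The article condenses a fuller protocol, which may hold a fallback.** That is possible. The point here, however, is a condition that is printed and, if followed, conflicts with other printed rules.

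**Severe spasticity is excluded and the ramp is gentle.** Both may reduce failures, and neither shows that they are rare. The article itself foresees participants who cannot follow the training protocols because of pronounced ankle flexor spasticity (Exercise protocols).

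**MMRM may recover some information.** Participants with one valid visit may still contribute, so complete-pair figures may overstate the loss. But MMRM relies on data missing at random, and would not repair missingness that depends on the effort not reached.

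A reader might infer more than the documents support:

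- *That many tests will have no primary outcome.* No attainment rate is given. Multiplying assumed pass rates for the three criteria would not supply one, because all three track effort in the same test and are unlikely to be independent.
- *That the comparison between arms is biased.* Baseline failures precede allocation and cannot bias it. At T4, unblinded participants who trained at 95% or at 60% of peak heart rate could differ in how near to maximum they go. That is only a possibility, of unknown size and direction, and outcome assessors are blinded.
- *That the rule explains the whole distance from 80% power.* Power is already about 66% at 52 completers.

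**Conclusion.** The point holds as a defect in the definition of the primary outcome. As printed, a correctly conducted test can produce no V̇O2peak, contrary to stratification of all participants and to intention to treat, and no eligibility or withdrawal rule deals with the case.

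Failures are plausible given spastic paraparesis, deconditioning and EDSS up to 6.0, and would tend to occur in more disabled participants; this is an inference from the population described. A difference between arms is possible at T4 only.

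The size cannot be derived from the documents. The loss of about 8 to 22 points of power rests on the assumed 60 to 85% of completers with two valid tests, on analysis of complete pairs, and on the plan's f = 0.15 and correlation 0.6. It illustrates what is at risk and is not a forecast.

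**What to change.** 1. Define V̇O2peak as the highest 15-second average reached in each test, at T0 and T4, whether or not the three criteria are attained.
2. Keep the criteria as descriptors of test quality, and report attainment of each, and of all three, by arm and visit.
3. Add a sensitivity analysis in participants who meet all three at both visits, and present it as a selected subset.

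The cost is about one sentence in the outcome definition and one in the analysis section. Oxygen uptake, heart rate and perceived exertion are already recorded, so no new measurement is needed. The downside is that some submaximal tests enter the primary analysis and add noise; the reported attainment and the sensitivity analysis let readers judge how much that matters. The change should be fixed before outcomes are looked at by arm, including at the planned interim analysis. The article reports 23 participants recruited by March 2023, against an interim look at 31 (15 + 16).
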